#### Data analysis

For the RCT study, data analysis will be performed on an intention-to-treat basis. Baseline characteristics between the two study arms will be compared by t-test, chi-square or Fisher's exact test

where appropriate. A generalized estimating equation (GEE) model will be used to compare the differential changes on the outcomes across the time points T0, T1, T2 and T3 between the two study arms with adjustment for potential confounding variables. Baseline characteristics with p values < 0.25 for between-group difference will be considered as potential confounding variables. GEE model can account for intra-correlated repeated measures data and accommodate missing data caused by incomplete visits or dropout, provided that the data are missed at random, and thus are particularly suitable for intention-to-treat analysis without the need of imputation for missing data. All statistical analyses will be performed using IBM SPSS 23.0. All statistical tests will be two-sided and a p-value < 0.05 will be considered statistically significant. For the qualitative study, the audio-taped data will be transcribed verbatim. The investigation team will ensure accuracy of the transcription by cross-checking. Content analysis will be adopted to code the qualitative data on participants' perceptions and acceptability of the modelling-based narrative intervention. The analysis will also seek to understand why and how the study intervention influences patients' care-seeking behaviours. The codes units will be organised into categories and subcategories, which will be analysed for emerging themes. The trustworthiness of the qualitative analysis will be enhanced by audio-taping of the interviews, conducting an audit trail, involving two team members to code the qualitative data independently.

**Figure 1.** Study implementation protocol

[figure not shown]

**Figure 2.** Graphical presentation of the modelling-based narrative intervention protocol

[figure not shown]

**Table 1.** The storyline of the narrative video-based virtual heart attack experiencing session

**Background information of the model patient:** **[name]**, 58 year-old man, bus driver, non-smoker, with hypertension and hyperlipidaemia. He sustained a musculoskeletal injury over his chest region a week ago

| Time    | Scenario                                                                                                                                                                                                                                                                                                                                                                                                       |
|---------|----------------------------------------------------------------------------------------------------------------------------------------------------------------------------------------------------------------------------------------------------------------------------------------------------------------------------------------------------------------------------------------------------------------|
| 11:00pm | On a typical day, [name] has just finished a long shift of work and he is walking home from the bus terminal.                                                                                                                                                                                                                                                                                               |
| 11:18pm | While he is climbing up the staircase to his house, he suddenly experiences some strange feeling of pressure over his central chest, with profuse sweating and dizziness. The pressure feeling radiates to his left shoulder and jaw → first PAUSE for discussion                                                                                                                                       |
| 11:20pm | [name] arrives home and immediately sits down in the living room. The first thing that comes in to his mind is that he has just had a tiring long shift and has no time for dinner. The symptoms are likely to be due to stomachache or the previous musculoskeletal injury.                                                                                                                                |
| 11:40pm | He tried to take an antacid and a piece of bread to see if the symptoms would disappear. However, the chest discomfort persists and becomes more intense with the onset of shortness of breath after taking the medication and food. [name] starts to wonder whether the symptoms are originating from his heart. He is overwhelmingly terrified by such a possibility → second PAUSE for discussion |
| 11:50pm | [name] wakes up and notices her husband is sitting on the sofa looking very pale. After enquiring what is wrong with him, [name] expresses her concern that the symptoms may indicate a heart problem. She suggests [name] should go to the Accident and Emergency Department for treatment                                                                                                         |
| 11:55pm | [name] struggles to decide whether he should go to the Accident Emergency Department immediately or wait for a little while to observe the symptoms. Many concerns relating to going or not going to the hospital flash through [name] mind → third PAUSE for discussion                                                                                                                        |
| 00:10am | [name] decides to go to the hospital as the discomfort worsens. He struggles again to decide whether he should call the ambulance or take a taxi to the hospital → fourth PAUSE for discussion                                                                                                                                                                                                       |
| 00:15am | [name] activates the emergency medical service by calling 999.                                                                                                                                                                                                                                                                                                                                             |
| 00:25am | The ambulance arrives and [name] is transferred into the ambulance. When paramedic attempts to take the vital signs of [name], he suddenly becomes unconscious. The paramedic immediately initiates resuscitation and defibrillation for [name].                                                                                                                                                      |
| 00:30am | He regains consciousness upon arrival at the Accident and Emergency Department                                                                                                                                                                                                                                                                                                                                 |
| 00:35am | [name] is diagnosed with an acute heart attack. The doctor activates the clinical pathway of heart                                                                                                                                                                                                                                                                                                          |

|         |                                                                                                                                                                                                         |
|---------|---------------------------------------------------------------------------------------------------------------------------------------------------------------------------------------------------------|
|         | attack management.                                                                                                                                                                                      |
| 00:50am | [name] is sent to catheterisation laboratory for an emergency percutaneous coronary intervention.                                                                                                    |
| 02:00am | The procedure is completed and [name] is stabilised with two stents deployed at the site of the culprit lesion of a major coronary artery. He is sent to the cardiac care unit for close monitoring. |

**Table 2.** Scenarios for the booster session of the modelling-based narrative intervention

| Scenario | Information                                                                                                                                                                                                                                                                                                                                                                                         |
|----------|-----------------------------------------------------------------------------------------------------------------------------------------------------------------------------------------------------------------------------------------------------------------------------------------------------------------------------------------------------------------------------------------------------|
| 1        | Chan Tai Foon, 67-year-old lady, presenting with chest tightness and difficulty in breathing, which wakes her up at midnight. Her husband passed away 2 years ago and she lives alone.                                                                                                                                                                                                              |
| 2        | Chu Yiu Keung, 55-year-old man, a private banker with an extremely heavy workload. While he is giving a presentation of his proposal to an important client, he experiences the sudden onset of chest discomfort. The pain is so intense it causes him to be unable to continue with the presentation.                                                                                              |
| 3        | Lee Kam Ho, 69-year-old woman, presents with gradual onset of pain over the right side of the chest while she is heading to the kindergarten to pick up her grandson at 4pm. She has to prepare the dinner for her family every evening.                                                                                                                                                            |
| 4        | Tsang Chi Chiu, 37-year-old man, a policeman who exercise regularly. No family history of cardiac disease. He presents with worsening chest tightness while he was exercising that week. The discomfort disappeared after a brief period of rest. While he is playing basketball tonight, he experiences the chest tightness again. However, this time, the pain persists despite a period of rest. |
| 5        | Wong Man, 82-year-old gentleman, presents with a gradual onset of dizziness and vomiting. He has type II diabetes, hypertension and coronary artery disease with stenting to 2 coronary arteries when he had a heart attack two years ago. At that time, he presented with sudden onset of severe chest pain.                                                                                       |

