### Study design

This is a sequential mixed-method study consisting of a randomised double-blind controlled trial and an exploratory qualitative study. The study implementation protocol is outlined in Figure 1. A research assistant (RA1) will recruit eligible participants from the cardiac clinics and wards of four regional hospitals in Hong Kong. The study sites are leading hospitals providing cardiac care services within the region. He/she will collect participants' baseline (T0) demographic data and study variables during a face-to-face interview. Block randomisation with a block size of 8, 10 or 12 will be used to ensure even distribution of participants between the two study groups. The block size and the respective allocation sequence to the intervention group receiving a modelling-based narrative intervention (by RA1) and control group receiving a didactic education (by RA2), will be determined by a computer-generated sequence. Participants chronologically recruited to the study will be allocated to the study groups by RA1 according to the computer generated sequence. Another independent RA (RA3), who is blinded to the study group allocation, will collect the post-intervention data. To detect short-term and long-term intervention effects, the outcome variables will be measured repeatedly at 3 (T1), 12 (T2) and 24 (T3) months following baseline data collection for both study groups. This extended period of outcome evaluation permits the study to detect the intervention effects on participants' actual care-seeking behaviours. Previous studies indicated that approximately 16% of these patients experienced AMI symptoms within two years. In the data collection telephone calls, the RA3 will enquire about whether the participants have been admitted to an emergency department with the experience of AMI symptoms. The study participants and their next of kin are strongly advised to contact the RA if they have been admitted due to a possible AMI attack.

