### Study participants

Patients will be eligible to join the study if they are (1)  $\geq 18$  years of age, (2) living in the community, (3) with a confirmed diagnosis of a prior AMI attack, (4) consent to participate and (5) those who can read Chinese. Individuals who do not understand Cantonese, with impaired communication ability, psychiatric problems or impaired cognitive functioning (i.e. Abbreviated Mental Test  $\leq 6$ ) which may hinder participation in the interventional activities will be excluded. For the RCT study, the sample size is determined on the basis of a large-scale RCT examining the effect of a brief nursing educational intervention on care-seeking knowledge, attitudes and beliefs related to AMI in people with CAD. The effect sizes for knowledge, attitudes and beliefs were 0.39, 0.24 and 0.23 at 3 months after the intervention. In consideration of both clinical relevance and previous study findings, the sample size of this study is determined to give the study adequate power to detect at least a small to medium effect size on the primary outcomes. Using PASS 13 (NCSS, Kaysville, USA), it is estimated that a sample size of 252 subjects per study arm would give the study 80% power at 5%

level of significance to detect an effect size as small as 0.23 on our primary outcomes between the control and intervention arms at the post intervention time points. Further allowing for a potential dropout rate of up to 20%, a total of 315 subjects per arm will be recruited. For the qualitative phase, a criterion sampling of 30 participants who have received the modelling-based narrative intervention will be invited to join on the basis of their prehospital delay time, which will be categorised into three groups:  $\leq 2$  hours,  $> 2$  and  $\leq 6$  hours, and  $> 6$  hours. The criterion is set according to the international AMI management guidelines, where such cut-offs are used to categorise patients into early, intermediate and late responders. A total of 30 participants will be recruited, with 10 participants for each category. Maximum variations in the sociodemographic and clinical profile of the participants will also be adopted in the sampling procedure to illustrate a wider range of data.

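### Covariates are chosen by baseline tests at p < 0.25, and the T0 score enters as a response rather than a covariate, which uses the baseline measurement inefficiently

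*Protocol*

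**What the plan says.** All references are to the protocol.

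- **Baseline tests (Data analysis).** "Baseline characteristics between the two study arms will be compared by t-test, chi-square or Fisher's exact test", where appropriate.
- **Covariate selection (Data analysis).** "Baseline characteristics with p values < 0.25 for between-group difference will be considered as potential confounding variables". No fixed covariate list is given.
- **Model (Data analysis).** A GEE will "compare the differential changes on the outcomes across the time points T0, T1, T2 and T3 between the two study arms", adjusted for the variables found by the rule above. T0 is one of four response times. The T0 score is not named as a covariate, and equal arm means at T0 are not stated as a constraint.
- **Allocation (Study design).** "Block randomisation with a block size of 8, 10 or 12 will be used to ensure even distribution of participants between the two study groups". Patients are recruited "from the cardiac clinics and wards of four regional hospitals in Hong Kong". Hospital is not named as a model term.
- **Sample size (Study participants).** 252 per arm, two-sided 5%, 80% power, for an "effect size as small as 0.23 on our primary outcomes between the control and intervention arms at the post intervention time points".

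**The concern.** There are two linked weaknesses.

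First, allocation is randomised, so any baseline difference between the arms is due to chance. A test of that difference says nothing about whether a variable predicts the outcome, and prediction is the reason to adjust in a randomised trial. Under the rule each characteristic has about a 25% chance of becoming a candidate, prognostic or not, and a strong predictor is passed over about 75% of the time. The adjustment set cannot be known until the data are in.

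Second, treating T0 as a response and testing the arm-by-time contrast amounts to comparing change scores. That comparison is less precise than one adjusted for the T0 score whenever rho is below 1. It also differs from the quantity for which the trial was sized, a between-arm difference after the intervention. At stake is power on the two primary outcomes, beliefs and attitudes, which could be regained from data already collected.

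**Working it through.** **Inputs.** From the protocol: 252 evaluable per arm, effect d = 0.23 SD, two-sided alpha 0.05, 80% power, T0 collected on everyone. Assumed: rho, shown from 0.3 to 0.7; and the number of baseline characteristics k, shown as 10 and 20. The protocol gives neither.

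**The plan's own figure.** For a plain post-intervention comparison of two means, n per arm = 2 × ((1.96 + 0.842)/0.23)² = 297, not 252. With 252 per arm the power at 0.23 is 73.3%; 252 corresponds to an effect of 0.25. The dropout step does reproduce: 252/0.8 = 315. The mismatch is a separate matter. It is noted here because 73.3% is the post-only benchmark below.

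**T0 as a response.** With equal variances over time, the variance of the between-arm contrast relative to the post-only comparison is:

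- post-only: 1
- change contrast: 2(1 − rho)
- adjusted for the T0 score: 1 − rho²

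The ratio of change to adjusted is 2(1 − rho)/(1 − rho²) = 2/(1 + rho), which exceeds 1 for every rho below 1. A simulated GEE with exchangeable correlation and complete data agrees that the arm-by-time estimate is the change-score difference.

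Power = Phi(0.23 × √126/√factor − 1.96), with 0.23 × √126 = 2.582. For example, at rho = 0.3 the change contrast gives 2.582/√1.4 − 1.96 = 0.22, or 59%. The adjusted analysis gives 2.582/√0.91 − 1.96 = 0.75, or 77%.

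| rho (assumed) | Variance ratio 2/(1+rho) | Power, change | Power, T0-adjusted | n per arm for 80%, change | n per arm for 80%, T0-adjusted |
|---|---|---|---|---|---|
| 0.3 | 1.54 | 58.8% | 77.2% | 416 | 271 |
| 0.4 | 1.43 | 65.4% | 80.4% | 357 | 250 |
| 0.5 | 1.33 | 73.3% | 84.6% | 297 | 223 |
| 0.7 | 1.18 | 91.5% | 95.1% | 179 | 152 |

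The change contrast equals post-only at rho = 0.5, because 2(1 − 0.5) = 1. Below 0.5 it is worse than ignoring T0; above 0.5 it is better.

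**Selection rule.** The number of characteristics passing p < 0.25 is roughly binomial(k, 0.25), treating them as independent. With k = 10, 2.5 pass on average (5th to 95th percentile 0 to 5), and the chance that at least one passes is 1 − 0.75¹⁰ = 94%. With k = 20, 5 pass on average.

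**Where the rule has an effect.** A time-constant covariate entered as a main effect cancels from within-patient change. In simulation (252 per arm, four times, complete data) the arm-by-time estimates with and without such a covariate agreed to about 10⁻¹⁶, and the standard error was 0.0769 either way. With dropout related to the covariate, intercept set for about 20%, the largest shift was about 0.02 SD. The group main effect did move, by up to 0.09 SD with complete data and 0.13 SD with dropout.

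**The case against.** **The change analysis matches the hypothesis.** The protocol hypothesises better changes in the intervention arm, and a change comparison is unbiased under randomisation. Both statements are true. However, adjusting for T0 estimates the same treatment effect in a randomised trial with less variance, so matching the hypothesis does not remove the gain.

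**The protocol does not say that the T0 means are free.** A GEE with T0 as a response and a common T0 mean would fit its wording and would recover the lost efficiency. A statistical analysis plan may set this. That stands as a limit: the power loss applies to the model as it would ordinarily be read and fitted. The p < 0.25 rule is different, because the protocol states it outright.

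**The loss depends on an unknown rho.** This stands. At 0.7 the gap is under 4 percentage points, and the change contrast then beats post-only. It would be too strong to say that the T0 score is wasted.

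**Two stronger readings a reader might infer.** One is that the p < 0.25 rule distorts the type I error or power of the primary test. In a post-score model with a strongly prognostic covariate, the rule makes the test conservative and less powerful than always adjusting. But the protocol plans a differential-change contrast, which such covariates leave unchanged for a continuous score with complete data. Even in the post-score model the effect is negligible for weak predictors: with 2% of variance explained, power is 73.1% under the rule and 73.6% with fixed adjustment. The other is that the rule biases the result or inflates false positives; nothing in the protocol or the calculations supports that. The wording also describes candidates, so 25% is the chance of being considered rather than of certain entry.

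**Conclusion.** The point holds as one of efficiency and pre-specification, not validity. As stated, the change contrast needs 18% to 54% more variance to be overcome than a T0-adjusted analysis, for rho from 0.7 down to 0.3. In power at 252 per arm and d = 0.23 the cost is about 18, 15, 11 and 4 percentage points at rho 0.3, 0.4, 0.5 and 0.7. Below 0.5 the planned contrast is also noisier than the post-intervention comparison that the sample size addresses. These figures rest on the assumed correlations, equal variances over time, complete data and unconstrained T0 means.

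The p < 0.25 rule is poorly founded in a randomised trial, but its reach is narrower. It mainly affects any group main effect that is reported, the outcomes seen only in patients with an event (ambulance use and prehospital delay, with about 16% expected to have symptoms within two years), and the discretion left to the analyst once the data are known.

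**What to change.** In the Data analysis section:

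1. Remove the between-arm baseline tests and the p < 0.25 rule. Show baseline characteristics by arm descriptively.
2. Pre-specify the model for the continuous scores: T1, T2 and T3 as responses, with arm, time, their interaction and the T0 score as covariate. Alternatively, keep T0 as a response with one common mean for both arms.
3. Add a short fixed list of covariates already collected, such as hospital, age and sex, chosen before outcome data are seen. Name the covariates for ambulance use and prehospital delay in the same way, keeping that list short because few patients will contribute.
4. State that the effect estimated is the between-arm difference at each follow-up time, so that the analysis and the sample-size statement address the same quantity.

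The cost is a change of wording in the protocol or the statistical analysis plan before the outcome data are examined. No new data or visits are needed.

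### The protocol takes missing at random as enough for GEE without imputation; unweighted GEE in general needs more, and arm-specific dropout could distort the primary contrast

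*Protocol*

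**What the plan says.** The protocol's Data analysis section plans an intention-to-treat analysis with a GEE model "used to compare the differential changes on the outcomes across the time points T0, T1, T2 and T3 between the two study arms", adjusted for baseline characteristics that differ between arms at p < 0.25. It says that GEE can "accommodate missing data caused by incomplete visits or dropout, provided that the data are missed at random", and draws from this that the method is "particularly suitable for intention-to-treat analysis without the need of imputation for missing data". It mentions no weighting and names no working correlation.

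Under Study participants, the sample size allows for loss to follow-up: "Further allowing for a potential dropout rate of up to 20%, a total of 315 subjects per arm will be recruited". The design effect is 0.23 SD. The primary outcomes are the care-seeking beliefs and attitudes scores, with knowledge as a secondary score. All three are measured at baseline and at 3, 12 and 24 months (T0 to T3).

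**The concern.** Validity under missing at random without imputation is a property of likelihood-based mixed models, not of ordinary GEE. The protocol assigns it to GEE and uses it to rule out imputation. This is a stated reason with an analysis decision attached, not a detail left open, so an analysis plan that follows the protocol would inherit both.

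Missing at random allows dropout to depend on earlier observed scores. In the planned model those scores, T0 included, are responses rather than covariates. Dropout that depends on them is therefore not covered by the baseline adjustment. If that dependence differs between the arms, the estimated difference can move away from the truth under the very assumption the protocol names. Because the design effect is only 0.23 SD, a shift of less than 0.1 SD is a large fraction of it.

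**Working it through.** **Inputs from the protocol.** Effect 0.23 SD; 252 per arm needed and 315 recruited; dropout up to 20%; visits T0 to T3.

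**Assumed, since the protocol gives no figures.** Dropout is monotone and depends on the last observed score, with a log-odds slope of 0.5 to 1 per SD. Within-patient correlation is exchangeable at 0.4 to 0.6, or autoregressive at 0.7.

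**1. The plan's own dropout figure.** 252 / (1 − 0.20) = 315, which reproduces. This allowance restores the number of patients; it does nothing about bias. (Whether 252 follows from 0.23 is a separate question, and nothing here depends on it.)

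**2. Why missing at random is not enough.** GEE solves Σ D′V⁻¹(Y − μ) = 0 over the observed values. For this to be centred at the true μ whatever V is, the mean of Y among those still observed must equal μ, given the covariates. That holds when data are missing completely at random or missingness depends on covariates. It fails when low or high scorers leave. If V is close to the true covariance and the outcome is continuous, its off-diagonal terms use the earlier residuals to correct for who left. If V is independence, no correction is made.

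**3. Size by hand, independence working correlation.** With a separate mean for each arm and visit, the T3 estimate is the mean C of those still seen. Let M be the mean of the whole arm and L the unseen mean of the leavers.

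- M = 0.80·C + 0.20·L, so C − M = 0.25·(M − L).
- Suppose leavers would have averaged 0.32 SD below their arm's mean. Then C − M = 0.25 × 0.32 = 0.08 SD.
- In the intervention arm only: 0.23 + 0.08 = 0.31. In the control arm only: 0.23 − 0.08 = 0.15.
- In both arms alike: 0.23 + 0.08 − 0.08 = 0.23.

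The relative error is 0.08 / 0.23 = 35%. The standard error of a simple two-arm comparison is √(2/252) = 0.089 SD. The expected z is 0.23/0.089 = 2.6 at the truth, 0.31/0.089 = 3.5 if inflated, and 0.15/0.089 = 1.7 if diluted, which is below 1.96.

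**4. Simulation of the T3 contrast (true value 0.23, about 20% dropout by T3).**

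Trial-sized runs: 315 per arm, 150 runs per scenario, slope 0.7 in one arm only, Monte Carlo standard error 0.007 to 0.008. The two values in each cell are for dropout linked to score in one arm or in the other.

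| True correlation | Independence GEE | Exchangeable GEE | ML mixed model |
|---|---|---|---|
| Exchangeable 0.5 | 0.304 / 0.156 | 0.236 / 0.227 | 0.234 / 0.228 |
| AR 0.7 | 0.309 / 0.165 | 0.230 / 0.248 | 0.241 / 0.237 |

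Large-sample runs: 400,000 per arm, true correlation exchangeable, 0.4 to 0.6.

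| Dropout mechanism | Independence | Exchangeable | AR(1), wrong structure |
|---|---|---|---|
| Completely at random | 0.226–0.233 | 0.227–0.233 | 0.226–0.233 |
| Same slope in both arms | 0.226–0.228 | 0.227–0.228 | 0.229–0.230 |
| Slope −0.5, one arm | 0.273–0.297 | 0.231–0.234 | 0.252–0.257 |
| Slope −1, one arm | 0.311–0.346 | 0.235–0.237 | 0.276–0.280 |
| Slopes −1 and +1 | 0.005–0.075 | 0.225–0.228 | 0.146–0.151 |

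Independence GEE fails whenever the mechanism differs by arm. Exchangeable GEE stays within 0.225 to 0.248 throughout. AR(1) drifts when its structure is wrong, most clearly under the steeper or opposite slopes. The mixed model stays within 0.228 to 0.241 in the runs where it was fitted.

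**The case against.** The strongest reply accepts that the sentence is too broad and disputes the consequence.

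- **The large errors need an independence working correlation, which the protocol does not choose.** This stands. The choice may well be in an analysis plan not shown here, and exchangeable GEE performed about as well as the mixed model. A reader might infer that the planned analysis is biased; the document does not support that. One permitted version of it can be.
- **The bias needs dropout to depend on earlier scores differently by arm.** This stands too. A reader might infer from the uneven burden (three weekly sessions and a booster against a single session) that such dropout is likely. But skipping a session is not missing an assessment. Outcomes are collected on the same schedule in both arms by a separate, blinded assistant, and attendance is recorded on its own. Arm-specific dropout is possible, and nothing in the protocol puts a figure on it.
- **20% is a ceiling, and a bias of about 0.08 SD is under one standard error (0.089 SD).** Both are true. But bias does not average out, and 0.08 is about a third of the effect the trial is designed to find.
- **The point might seem to extend to ambulance use, or to call for a sensitivity analysis for data missing not at random.** Neither follows. Ambulance use exists only for participants with a symptom episode, which the protocol puts at roughly 16% over two years. For the rest there is no value to impute or weight for. Missing not at random is a different assumption from the one misstated here.

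What the reply does not rescue is the sentence itself. It presents missing at random as sufficient, without the conditions that would make it so, and sets imputation aside on that ground.

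**Conclusion.** The protocol misstates what unweighted GEE needs, and its case for doing without imputation rests on that misstatement. This part is certain and does not depend on any simulation.

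The numerical consequence is conditional. With about 20% dropout, a score-dependence of 0.7 log-odds per SD in one arm only, and an independence working correlation, a true 0.23 SD at T3 is estimated as about 0.15 to 0.31. Steeper or opposite mechanisms widen that range. With an exchangeable working correlation the estimate stays near 0.23. With AR(1) it does so in most scenarios, but not when the structure is wrong and the mechanisms are strong. If dropout works alike in both arms, the bias in the contrast is about zero. The correlations and slopes are assumptions.

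The sponsor should correct this, because the remedy is cheap. It is not evidence that the trial's result will be wrong.

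**What to change.** For beliefs, attitudes and knowledge, make the analysis a likelihood-based mixed model for repeated measures over T0 to T3, with arm, visit and arm-by-visit terms and an unstructured covariance. That analysis is valid under the missing-at-random assumption the protocol already makes. It uses the same data and can be fitted in SPSS, the software already named.

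In either case, rewrite the sentence on GEE. It should say that unweighted GEE is in general valid when data are missing completely at random or missingness depends on modelled covariates, and that under missing at random it also needs weighting, imputation or a near-correct working correlation.

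If GEE is kept for these scores, prespecify a non-independence working correlation and add multiple imputation or inverse-probability weighting. The mixed-model route costs a few lines of analysis text, with no change to sample size, visits or data collection. The GEE route adds an imputation or weighting model to specify.
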